- k Blood sample (15mL on day-1 & 28, month 3, 6, and 12; 10mL on days 3, 7, 14, 21, 42) for anti-SARS-CoV-2 antibody titre (serum), cytokine/chemokine, inflammation and disease severity biomarker panel (serum), CyTOF for B and T cell markers (fixed whole blood), transcriptomics (gene expression), malaria and non-malaria serology (serum), malaria microscopy, malaria and non-malarial pathogen detection by molecular (e.g. PCR & TaqMAN, RDT), and (in malaria positive participants) genotyping to differentiate between recrudescence or reinfection (whole blood), biochemistry (day-1 and day-28 only), full blood count for haematology (day-1 & 28 only, or when clinically indicated), host genetics (blood pellet/dried blood spots) and QuantiFERON-TB Gold In-Tube (whole blood, at enrolment or otherwise at any other timepoint after enrolment if the QuantiFERON was missed at enrolment; a repeat QuantiFERON sample will be taken at 12m for all). In children, the total volume of blood will be 2.5mL in children weighing <10kg and 5mL in children weighing 10-<15kg.
- l Blood sample for serology and for malaria microscopy and RDT. The day-21 & 42 visits are in the nested malaria treatment trial only.
- m Stool sample for detection of helminth infection, SARS-CoV-2 detection and culture.
- n Informed Consent procedures, randomization and initiation of malaria treatment may also occur on day 0 if participants test positive for malaria during the cross-sectional screening for SARS-CoV-2 by routine staff and by a SARS-CoV-2 antigen test (see d, g, above). If the SARS-CoV-2 test results turn out to be negative, the patient will complete the 3-day treatment course as assigned but will be considered a screening failure and not followed-up any further.
- o Study drug: ## denotes either artemether-lumefantrine (AL) twice daily, or pyronaridine-artesunate (PA) once daily (depending on group assignment). The first dose will be administered in the study clinic as directly observed therapy. All subsequent doses will be taken at home by the study participant if they are asked to self-isolate for home-based care, or by study/hospital staff for participants admitted to isolation wards.

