## 6.2.2 COVID-19 cohort study

### 6.2.2.1 Inclusion criteria

- Laboratory confirmed SARS-CoV-2 infection, with positive molecular test results within the past 72 hours\* or a positive rapid diagnostic antigen test
- Aged  $\geq 6$  months \*\*
- Resident in the study area
- The participant or caretaker is willing and able to give informed consent or assent with parent/guardian informed consent for participation in the study
- Agrees not to self-medicate with chloroquine, hydroxychloroquine or other drugs with potential anti-SARS-CoV-2 properties without prior discussion with medical study staff
- Contactable by phone for follow-up permitting real-time, reliable information

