## 6.2.3 Nested malaria treatment trial

### 6.2.3.1 Inclusion criteria

- Fulfills all inclusion criteria for the COVID-19 cohort study
- Uncomplicated malaria, defined as able to take oral medication
- Bodyweight  $\geq 5$ kg
- Confirmed malaria infection by RDT (HRP2 or pLDH) or microscopy

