### 9.1.1 Pre-screening with point of contact (POC) SARS-CoV-2 antigen tests

The screening study (cross-sectional survey, source population) includes pre-screening with an experimental POC SARS-CoV-2 antigen tests and Government approved antigen tests. At the time of writing (September 2020), there are no approved SARS-CoV-2 antigen tests yet in Kenya or Burkina, but this may change during the course of the study. We will follow the national guidelines in each country. In Kenya GeneXpert, antigen-RDT and PCR results are considered for definitive diagnosis of COVID-19. If a participant tests COVID positive for any rapid antigen tests, GeneXpert, or PCR, the participant shall be enrolled.

Eligible patients with both a positive SARS-CoV-2 test and a positive malaria test on Day-0 require malaria treatment that same day and will be invited to enrol in the COVID-19 cohort study and the nested malaria treatment trial on Day-0; i.e. prior to knowing the SARS-CoV-2 PCR results (see 9.2.1.3, Nested malaria treatment trial, page 43). Patients with a positive antigen test but negative for malaria will be invited to participate in the COVID-19 cohort study and can choose whether to enrol that same day (Day-0) or wait until the confirmatory PCR results become available (typically on Day-1).

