### 11.2.2.2 Malaria treatment study

For the nested malaria treatment trial, the primary analyses will be based on the Intention-to-treat (ITT) population and secondary supportive analyses will be done on the Per-protocol (PP) population. The safety analysis will be performed on the safety population. These analytical populations are defined as follows: 1) The ITT population consists of all randomised subjects with valid informed consent; 2) The PP population is a subset of the ITT population, where subjects with major protocol deviations will be excluded. Major protocol deviations will be defined in the Statistical Analysis Plan (SAP). 3) The safety population is a subset of the ITT population, consisting of all randomised subjects who receive at least one dose or a partial dose of study drug.

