### 11.2.5.4 *Safety analysis*

For the safety analysis, data from all subjects from the safety analysis population will be included. All analyses will be descriptive. Data will be summarized by treatment group. The percentage of subjects with at least one AE during the follow-up period will be tabulated with exact 95% CI (two-sided). No multiplicity adjustment will be implemented in analysis. The percentage of subjects with at least one report of unsolicited AE and reported up to 28 days after enrolment will be tabulated with exact 95% CI.

The occurrence of SAEs will be determined on the safety analysis population. The proportion of subjects with an SAE, classified by the MedDRA preferred term level, reported from study start until study conclusion will be tabulated with exact 95% CI. Comparisons between groups will be made using Fisher's Exact Test for each preferred term. Serious adverse events (SAEs) occurring at any point during the trial will be summarised, and relatedness to treatment will be assessed.

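### Footnote n labels participants already randomised and dosed as screening failures, although a positive antigen test made them eligible, and stops their adverse-event follow-up

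*Protocol*

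**What the plan says.** Footnote n of 2.2.4 lets consent, randomisation and the first dose take place on Day 0 when the patient is positive for malaria and on a SARS-CoV-2 antigen test. If the SARS-CoV-2 result then turns out negative, "the patient will complete the 3-day treatment course as assigned but will be considered a screening failure and not followed-up any further". The footnote does not name the later test. A positive antigen test was already needed to get this far, so it can only be a subsequent one, in practice the PCR.

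Other sections bear on the same people:

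- **Cohort eligibility (6.2.2.1):** a recent positive molecular test "or a positive rapid diagnostic antigen test".
- **Nested-trial eligibility (6.2.3.1):** "Fulfills all inclusion criteria for the COVID-19 cohort study", with no added requirement for PCR.
- **Enrolment (9.1.1):** "If a participant tests COVID positive for any rapid antigen tests, GeneXpert, or PCR, the participant shall be enrolled". Patients positive for both infections are invited into the trial on Day 0, "prior to knowing the SARS-CoV-2 PCR results".
- **Analysis populations (11.2.2.2):** "The ITT population consists of all randomised subjects with valid informed consent". The safety population is a subset of this, "consisting of all randomised subjects who receive at least one dose or a partial dose of study drug".
- **Safety analysis (11.2.5.4):** "data from all subjects from the safety analysis population will be included", and the percentage with at least one adverse event is tabulated.
- **Safety endpoint (4.3):** treatment-related events, serious events and events leading to discontinuation, cumulated to day 7.
- **Stopping study drug (8.1.1):** those who stop the drug stay in the study and keep their scheduled evaluations.

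**The concern.** A person who has been randomised and has swallowed study drug is past screening. Under the entry criteria, a person positive by antigen is also eligible, so the label in footnote n is wrong on the protocol's own terms.

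The practical harm lies in the second half of the instruction. Someone who completes the full course under footnote n gets less safety follow-up than someone who abandons the drug under 8.1.1. The missing period matters for pyronaridine-artesunate. The product information in Appendix VII describes transaminase rises that peak between days 3 and 7, and 7.2.2.2.1 asks for particular watchfulness over the first two weeks.

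These people stay in the safety denominator. With nobody asking about events, they count as event-free after the cut-off, and the adverse-event percentages are understated. A statistical analysis plan can redefine a population, but it cannot recover assessments that were never made.

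**Working it through.** **1. What is lost per affected participant.** The adverse-event row of the nested trial in 2.2.4 is marked in 11 windows: days 1, 2, 3, 4–6, 7, 8–13, 14, 15–20, 21, 28 and 42. Five of these run up to day 7. Section 9.1 puts the usual turnaround at 18 to 48 hours, that is, day 1 or day 2. The footnote can be read in two ways:

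| Follow-up ends | Windows lost (of 11) | Lost up to day 7 (of 5) |
|---|---|---|
| on a day-1 result | 10 | 4 |
| on a day-2 result | 9 | 3 |
| after the 3-day course | 8 | 2 |

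At this turnaround the day-7 assessment is lost on both readings. Of the six mid-nasal swabs (days 1, 3, 7, 14, 21, 28), five are lost if follow-up ends at the result and four if it ends after day 3. The day-7 swab is lost either way.

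**2. Effect on the adverse-event percentages.** Let f be the share of the safety population affected. The protocol does not give f, so 5% and 10% are assumptions: 0.05 × 142 ≈ 7 people and 0.10 × 142 ≈ 14. If none of their events were recorded, the reported percentage would be the true percentage × (1 − f), or 0.95 and 0.90 of the truth. This is an upper bound, because events before the cut-off are still captured.

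**3. The stated power.** Section 11.1.3 gives 80% power for 20% versus 42.2% day-7 clearance, with 134 completers (67 per arm) and two-sided alpha 0.05. With n per arm, pooled variance and no continuity correction:

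power = Φ{[Δ√n − 1.96√(2p̄(1 − p̄))] / √(p₁(1 − p₁) + p₂(1 − p₂))}

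Here Δ = 0.222, p̄ = 0.311 and n = 67. The numerator is 1.817 − 1.283 = 0.534 and the denominator is 0.636, so power = Φ(0.840) = 79.96%. The stated figure reproduces.

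**4. Dropping or keeping these participants in the primary analysis.** Two cases use the same formula:

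- *Dropped:* completers fall to 134(1 − f).
- *Kept:* assume that all of them are swab-negative on day 7 in both arms. The rates become 0.20(1 − f) + f and 0.422(1 − f) + f, with 67 per arm.

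| Assumed f | Power if dropped | Rates if kept | RR if kept | Power if kept |
|---|---|---|---|---|
| 0 | 80.0% | 20.0% vs 42.2% | 2.11 | 80.0% |
| 5% | 77.9% | 24.0% vs 45.1% | 1.88 | 73.3% |
| 10% | 75.6% | 28.0% vs 48.0% | 1.71 | 66.7% |
| 20% | 70.5% | 36.0% vs 53.8% | 1.49 | 54.3% |

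On this worst-case assumption, keeping false-positive participants costs the virological comparison more power than dropping them. The safety argument and the efficacy argument therefore point in different directions and need separate rules.

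**The case against.** The rule has an understandable origin. When 9.1.1 was written, no antigen test was approved in either country. Appendix IX (16.9.1) treats the novel tests as experimental and as a trigger for confirmation, and footnote a calls the PCR confirmatory. The amendment description records that antigen eligibility was added in version 2.0. Footnote n therefore looks like wording that was not updated, more than a deliberate design choice. This stands as an explanation, but the footnote is current text and sites will act on it.

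The exposure is also limited. Both drugs are approved in both countries (12.2.4). Serious events and pregnancies that come to staff attention are still reported (10.10.4), and participants are told how to reach the team (9.2.1.2). That stands too, and it keeps the point moderate. It does not replace planned assessment of a day-7 endpoint.

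A reader might go further in three ways that the documents do not support:

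- **That the footnote removes people from the ITT or safety population.** It does not say so. Under 11.2.2.2 they remain members, and what they lack is data. A missing day-7 swab then falls under the complete-case rule of 11.2.6.2.
- **That the day-7 assessment and swab are always lost.** Footnote e allows slower results, and 6.2.2.2 allows up to 120 hours at delayed sites. One version of the schedule header opens the day-7 window two days early. With a day-5 result, the day-7 visit could already have taken place.
- **That the arms would become unbalanced.** The later result appears to come from the Day-0 screening swab, taken before randomisation, so no difference between arms is expected.

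**Conclusion.** The point holds as a conflict of wording and a gap in safety follow-up, and it should be corrected. Calling an antigen-positive participant a screening failure contradicts the entry criteria. Stopping follow-up leaves members of the stated safety population without 8 to 10 of 11 planned assessments, including day 7, when results arrive at the typical 18 to 48 hours.

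The overall effect cannot be sized from the protocol. The number affected is not given and may be small. If 5% to 10% were affected, the adverse-event percentages would be understated by at most the same relative amount, in both arms alike.

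The efficacy side gives no case for simply retaining these participants in the primary analysis. If all of them are swab-negative on day 7, retention lowers power to about 73% or 67% at an assumed 5% or 10%, against 78% or 76% if they are dropped.

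**What to change.** 1. In footnote n, delete the screening-failure label and the instruction to stop follow-up.
2. State that every randomised participant who took any study drug stays under telephone follow-up for adverse events, serious events and pregnancy, at least to day 7 and preferably to day 28, whatever the later PCR result. The calls already planned in 9.2.3 cover days 2, 4–6, 8–13 and 15–27. Days 3, 7 and 28 are visits, so a call can take their place. Virology, serology and pharmacokinetic sampling may stop.
3. Fix separately how antigen-positive, PCR-negative participants enter the virological primary analysis. One option is an analysis set defined only by the pre-treatment baseline swab and applied identically in both arms. The other is the full ITT population with a sensitivity analysis limited to participants whose baseline swab was positive. The research swab taken at enrolment (9.2.1.2) can serve if it is taken before the first dose. Collecting day-7 swabs from these participants is needed only under the second option.

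The cost is an amended footnote, one or two sentences, and a few extra phone contacts with participants who may add nothing to the virological endpoint.

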#### 11.1.1 Cohort

The primary endpoint used for the sample size calculations is the cumulative proportion of patients that progresses at least one category in disease severity from enrolment to day-28 based on the WHO clinical progression scale (see 16.4, Appendix IV. WHO clinical progression scale, page 82). At least one category increase in disease severity is defined as progressing from either asymptomatic or mild disease at enrolment to at least moderate disease requiring hospital admission (excluding hospitalisations for isolation only), or from moderate disease at enrolment to severe disease, or from severe disease at enrolment to death. For definitions of each disease severity category, see 16.4, Appendix IV. WHO clinical progression scale, page 82. The sample size calculations to determine the crude impact (i.e., unadjusted for potential confounders) of malaria on COVID-19 disease regression suggests that a pooled sample size of 708 (673 completers) of whom approximately 142 are malaria positive and 566 are malaria negative (135 and 538 completers) would provide 90% power to detect a 50% difference in the primary endpoint from 30% in the malaria-negative group to 45% in the malaria positive group ( $\alpha=0.05$ , 5% loss to follow-up by day 28). The true power is likely to be lower when the confounding effect of baseline differences between malaria and non-malaria patients (such as age is considered). However, the inflation in the sample size required is difficult to estimate a priori. Similar crude sample size calculations using 80% power suggest 522 participants are required. Thus overall, a sample size of 708 participants would provide 80% power to detect a 50% difference in the primary endpoint allowing for a 35.6% inflation in sample size ( $708/522=1.356$ ) to take adjustment for confounding into account in multivariate or stratified analysis. The sample size calculation for the COVID-19 cohort study assumes that each country will recruit 354 COVID-19 participants and that approximately 20% of them are coinfecting with malaria (RDT positive), representing a weighted average of 15% of 354 COVID-19 cases in Kenya and 25% of 354 cases in Burkina Faso.

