## 11.2.2 Populations for analysis

### 11.2.2.1 Screening study (cross-sectional survey source population) and COVID-19 cohort study

All participants in the screening study (cross-sectional survey, source population) and COVID-19 cohort study will contribute to the analysis of the associations with malaria and COVID-19 prevalence and severity.

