If these tests perform with high accuracy (WHO Target Product Profile [TPP] to be published in July) in sub-Saharan Africa, they could be implemented for diagnostic purposes, to speed time to diagnosis for triage, treatment, isolation and in clinical trials to speed time to recruitment. For this study, all these tests will be considered experimental and will not be used for patient care but may trigger expedited confirmation by diagnostic tests that are approved in each country, such as qPCR. This may change during the study when more tests are approved in each country.

*Sample size:* Approximately, 1000 suspected or confirmed COVID-19 cases from the screening study (cross-sectional survey, source population) and COVID-19 cohort study.

*Methods:*

**Molecular diagnostics:** Saliva samples (250 µL minimum), will be collected and half extracted for RNA, the other half to be used directly on the LAMP reaction. Time to results is 20 minutes using this direct method of amplification.

**Antigen testing:** Direct sampling of saliva from the patient's mouth with a Biosure/Mologic antigen test (like HIV self-test) device. The device will sample approximately 100 µL, and results read on a lateral flow device within 15 minutes.

**Antibody testing at the point of contact:** 10ul of serum will be applied to the test pad and results read after 10 minutes for IgA, IgM and IgG.

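### Schedule footnote n contradicts the enrolment rules and the ITT definition: its removal of antigen-positive patients with a later negative result covers only those with malaria, which can bias the malaria comparison

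*Protocol*

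**What the plan says.** **Entry.** The cohort inclusion criteria (section 6.2.2.1) accept a recent positive molecular test "or a positive rapid diagnostic antigen test". The pre-screening criteria (section 9.2.1.1) likewise count infection as confirmed by either method. Section 9.1.1 treats antigen, GeneXpert and PCR results in Kenya as definitive and adds: "If a participant tests COVID positive for any rapid antigen tests, GeneXpert, or PCR, the participant shall be enrolled".

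**Malaria-positive patients.** Under footnote n of the schedule (section 2.2.4), consent, randomisation and first treatment "may also occur on day 0 if participants test positive for malaria during the cross-sectional screening for SARS-CoV-2" and also have a positive antigen test. If the SARS-CoV-2 result later proves negative, the patient "will be considered a screening failure and not followed-up any further".

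**Malaria-negative patients.** Under section 9.1.1, antigen-positive patients without malaria "can choose whether to enrol that same day (Day-0) or wait until the confirmatory PCR results become available (typically on Day-1"). Nothing is written about those who enrol on Day 0 and later have a negative PCR.

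**Analysis.** Section 11.2.2.1 states: "All participants in the screening study (cross-sectional survey, source population) and COVID-19 cohort study will contribute to the analysis" of malaria and COVID-19. It defines no PCR-confirmed set. For the nested trial, section 11.2.2.2 defines ITT as everyone randomised with valid consent, and section 11.2.6.2 makes the primary analysis complete-case.

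**Status of the antigen tests.** Appendix IX (section 16.9.1) says that "all these tests will be considered experimental and will not be used for patient care", while allowing that this may change as tests are approved. That sits uneasily with section 9.1.1.

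**The concern.** The same patient is a valid enrolee under sections 6.2.2.1 and 9.1.1 and a screening failure under footnote n. The footnote covers only malaria-positive patients, so the one written removal rule depends on malaria status, which is the exposure in the cohort's primary comparison. That endpoint is "the cumulative proportion of patients that progresses at least one category in disease severity from enrolment to day-28". If antigen-positive, PCR-negative patients progress at a different rate from PCR-confirmed cases, keeping them in one malaria group and dropping them from the other moves the risk ratio away from its true value.

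Clearance is exposed too. It is defined by negative nasal swabs, and PCR-negative patients would be expected to count as cleared. Keeping them among malaria-negatives only would make clearance look faster there.

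In the nested trial, the footnote ends follow-up of people already randomised, contrary to the ITT definition. A statistical analysis plan cannot recover visits that never took place.

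**Working it through.** **1. The plan's own figure.** Inputs from section 11.1.1: 30% versus 45%, 538 and 135 completers, two-sided alpha 0.05, 5% loss. The pooled two-proportion z-test gives power 90.3% (stated 90%). At a 4:1 ratio, 90% power needs 134 × 5 = 670 completers, or 670/0.95 = 706 enrolled (stated 673 and 708). For 80% power, 99 × 5 = 495 and 495/0.95 = 522 (stated 522). The sample size reproduces, so the issue lies only in who is retained.

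**2. Share of antigen positives that are PCR-negative (f).** The protocol gives no figure. I assume sensitivity of 70–80% and specificity of 97–99%, and take the 20% positivity of section 11.1.4 as prevalence:

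f = 0.8(1 − spec) / [0.2·sens + 0.8(1 − spec)]

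- Sensitivity 80%, specificity 99%: 0.008/0.168 = 4.8%.
- Sensitivity 70%, specificity 97%: 0.024/0.164 = 14.6%.

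**3. Risk in each group with no malaria effect.** Confirmed cases progress at 30% in both groups. Footnote n is taken as followed, so malaria-positives are all confirmed and their risk is 0.30. Let w be the share of malaria-negatives who enrol on the antigen result (the rest wait, and those PCR-negative do not enter). Let r be the progression risk of PCR-negatives relative to confirmed cases. Neither w nor r is in the protocol. Then:

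g = wf / (wf + 1 − f); p_neg = 0.30(1 − g) + 0.30·r·g; RR = 0.30 / p_neg

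**4. Worked case (f = 10%, w = 1, r = 0).** p_neg = 0.30 × 0.90 = 0.27 and RR = 0.30/0.27 = 1.11. The pooled proportion is (135 × 0.30 + 538 × 0.27)/673 = 0.276. The null standard error is √[0.276 × 0.724 × (1/135 + 1/538)] = 0.0430, so the critical difference is 1.96 × 0.0430 = 0.0843. The actual standard error is √(0.21/135 + 0.1971/538) = 0.0438. The upper tail is P(Z > (0.0843 − 0.03)/0.0438) = 0.108 and the lower tail 0.005, so two-sided rejection is 11.2% instead of 5%.

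**5. Range for f from 4.8% to 14.6%, with 538 versus 135 held fixed.**

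| w | r | RR under no effect | Two-sided rejection |
|---|---|---|---|
| 1 | 0 | 1.050–1.171 | 6.4–18.6% |
| 1 | 0.5 | 1.024–1.079 | 5.4–8.3% |
| 0.5 | 0 | 1.025–1.086 | 5.4–8.9% |
| 0.5 | 0.5 | 1.012–1.041 | 5.1–6.0% |
| 0.5 | 1.5 | 0.988–0.962 | 5.0–5.7% |
| any | 1 | 1.000 | 5.0% |
| 0 | any | 1.000 | 5.0% |

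**6. One rule for both groups.** If all are kept or all removed, with equal f and r, the null RR is 1.00 and rejection 5.0%.

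**7. Nested trial.** Section 11.1.3 plans 134 completers for 20% versus 42.2%; this reproduces at 80.0% power with 67 per arm. If 10% of randomised patients are dropped, power is 75.6%; at 20% it is 70.5%. The footnote applies alike to both arms, so the effect shown here is lost numbers, not bias between arms.

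**The case against.** The strongest objection is that differential removal is not established. It happens only if footnote n prevails over the inclusion criterion, section 9.1.1 and section 9.2.1.1. Section 9.2.1.3, on enrolment into the nested trial, repeats no such removal; its only limit on follow-up concerns malaria tests positive on the HRP2 band alone. If the enrolment sections govern, antigen-positive patients stay in both groups. The footnote also speaks of SARS-CoV-2 results without naming PCR, although section 9.1.1 describes this Day-0 enrolment as preceding the PCR result. And malaria-negatives may wait for PCR. All of this stands, and it makes the bias conditional.

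A reader might infer that false positives are removed only from the malaria-positive group and that malaria will therefore look harmful when it is not. The documents do not support that. A PCR-negative patient need not be uninfected, since the PCR may be falsely negative. The progression endpoint excludes admissions for isolation but is not limited to admissions caused by COVID-19, and the screened population includes people who may be ill from something else. Equal progression gives no bias, and higher progression reverses it.

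The scheduled Day-1 research swab would also allow a common PCR-positive set to be formed in both groups even with the footnote unchanged. That limits the harm in the cohort analysis, but it does not restore follow-up of the dropped patients or settle the conflict with ITT.

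**Conclusion.** The contradiction stands as written: footnote n conflicts with sections 6.2.2.1, 9.1.1 and 9.2.1.1 on who is enrolled, and with section 11.2.2.2 on who is analysed, and its removal rule depends on malaria status. The bias is possible, not certain. Taking f as about 5–15%, the null risk ratio runs from 1.05–1.17 (rejection about 6–19%) in the extreme case, through about 1.01–1.04 (5–6%) with half entering by antigen and PCR-negatives progressing half as often, to 1.00 if they progress equally or if all malaria-negatives wait and PCR-negatives are not enrolled. It falls below 1 if they progress more often. The 19% figure is a corner of the range. These sizes rest on assumed test accuracy, entry route and progression in PCR-negatives. The clearance comparison can be distorted whatever their progression rate, provided some PCR-negative patients stay in one group only.

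A reader might also conclude that the primary cohort analysis should be confined to PCR-confirmed participants. That goes too far: it would override an inclusion criterion that accepts antigen results and would drop true cases with a false-negative PCR.

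**What to change.** - Reconcile footnote n with sections 6.2.2.1, 9.1.1 and 11.2.2.2 so that one rule applies whatever the malaria status.
- Delete the end-of-follow-up consequence in footnote n for antigen-positive participants. Keep every antigen- or PCR-positive enrolee, including everyone randomised, in follow-up, and analyse all enrolled.
- Add a sensitivity analysis restricted to participants with PCR confirmation, by diagnostic PCR or the Day-1 research swab, with the same definition in both malaria groups.

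The cost is protocol wording and follow-up of a few more malaria-positive participants; the swabs are already planned. One limit remains. In the nested trial, retained patients who were never infected would be swab-negative on Day 7 in either arm, so keeping them honours ITT but does not regain the power in step 7. The PCR-confirmed sensitivity analysis shows how far they dilute the treatment contrast.
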